#### Randomization

We apply a stratified permuted block randomization for this study. Participants are classified into four strata based on the hospital codes (two hospitals) and the EPDS groups (lower EPDS: 0–8 points, the higher EPDS: ≥ 9 points). The biostatistician will create a stratified block random table, and the research assistant will allocate participants into either the intervention or TAU group according to the Table. A list of participants allocated to the intervention and TAU groups will be password-locked in the computer and will be blinded to the researchers.

### Statistical methods

#### Clinical efficacy

For primary outcomes, an analysis of covariance (ANCOVA) will be conducted to compare the mean differences of co-primary outcomes at 24 weeks follow-up between the intervention and TAU groups after adjusting baseline scores. The study sets two co-primary outcomes, including the EPDS scores at 24 weeks after the initiation of the program and psychological aggression toward children measured by the CTS-1 scores at the 24 weeks follow-up survey. The order of statistical testing is as follows: (1) the EPDS scores at 24 weeks follow-up; (2) CTS-1 scores at 24 weeks follow-up. If we find statistical significance for the EPDS scores at the predefined 0.05 level, then we will conduct statistical testing for the CTS-1 scores. If we do not find statistical significance for the EPDS scores, we will conduct the ANCOVA for the CTS-1 score as a complementary analysis. Given the fixed-sequence testing procedure, the study will not adjust for the multiplicity of each statistical test.

For secondary outcomes, the ANCOVA will be conducted to compare secondary outcome measures (Table 2) between the TAU and intervention groups after adjusting baseline scores. Statistical analyses will be performed using the SAS version 9.4 (SAS Institute, Cary, North Carolina, USA).

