## Background

Child abuse is a challenging issue in public health as it affects the physical, psychological, and social health outcomes of individuals for a lifetime [1–9]. From a societal perspective, child abuse imposes a substantial financial burden on societies as it creates high direct and indirect costs in low, middle, and high-income countries [10–12]. Existing research has identified the following characteristics as being associated with a higher risk for child abuse: parental depression, anxiety and anger-hyperactivity, parent stress, poor parent–child interactions, and low social support [13]. However, there is presently no solution for how to prevent child abuse right after birth.

Postnatal depression is another critical problem closely related to child abuse [14, 15]. Depression is the leading cause of disease-related disabilities among women [16, 17]. Previous studies indicated that women with postpartum depression were at higher risk for lower physical and psychological health, substance abuse, and suicidal behaviours [18–22]. Child abuse and postnatal depression often co-occur, and the rate of childhood maltreatment is highest during the first year of life [23, 24]. Children born to depressed mothers were at higher risk for prematurity, delayed physical, motor, and cognitive development [22]. Moreover, postnatal depression among mothers was associated with a significantly increased risk for harsh parenting, physical and psychological abuse [14, 15, 25–27].

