## Methods/design

### Objectives

The study is a 6-month follow-up stratified randomized controlled trial at multiple medical centres. A web-based behavioural activation program for smartphones with therapist support will be developed for postnatal mothers in Japan, based on a previous study [32]. The aims of the study are as follows:
To investigate the effect of an internet-based behavioural activation program on improving depressive symptoms and preventing abusive behaviours toward their children as co-primary outcomes, as well as parental stress, bonding relationship, health-related quality of life (QOL), and child developmental measures as secondary outcomes.To investigate how the medical and social characteristics of participants influence implementation aspects (acceptability, appropriateness, and feasibility). We have set two co-primary outcomes in this trial, as the effects on both mothers and children are equally important. The hypotheses of the study are as follows:

(H1) The web-based behavioural activation program for smartphones will significantly improve depressive symptoms 24 weeks after the initiation of the program among postnatal mothers with EPDS scores ≥9 points in the intervention group as compared to those in the TAU group; and.

(H2) The smartphone-based behavioural activation program will significantly prevent abusive behaviours toward children at 24 weeks after the initiation of the program among all the postnatal mothers in the intervention group as compared to those in the TAU group.

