### Inclusion criteria

Age ≥ 20 years old at recruitment (Age of adulthood is 20 years or older in Japan).Postnatal women who had given birth within 10 weeks of recruitment.Have regular internet-access via smartphones or other internet devices.Currently living with the new-born baby.Fluent in Japanese (Able to understand the content and work on the program).

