#### Sample size calculation

As the study has two co-primary outcomes, we calculated each sample size needed to improve the depressive symptoms of mothers and to prevent abusive behaviours toward children based on the effect size from a previous study.

The study reported the effect size of the internet-based behavioural activation for postnatal depression as d = 0.55 [32]. With a significance level of 0.05, the statistical power of 80%, and a follow-up rate of 85%, the sample size needed to detect efficacy for postnatal depression in the high EPDS group is 128 participants (64 participants for each arm). (Sample size calculation was carried out using the G*Power 3.1.9.2.)

No previous study examined the effect of iBA for preventing child abuse, so we used the effect size d = 0.56 of cognitive behavioural therapy for anger from a randomized controlled trial [64]. We estimated the effect size of the iBA for psychological aggression as d = 0.50 for the high EPDS group based on the previous study [64], and d = 0.40 for the low EPDS group. With a significance level of 0.05, the statistical power of 80%, and a follow-up rate of 80%, the required sample size is 150 participants for the high EPDS group (75 participants per arm) and 240 participants for the low EPDS group (120 participants per arm).

Finally, we expected the sample size needed to detect the change in both depressive symptoms and abusive behaviours would be 150 participants for the high EPDS group and 240 participants for the lower EPDS group.

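### The primary CTS-1 model appears to leave out baseline EPDS, although the plan itself treats initial depression as a stratifier, a risk factor and a dropout predictor

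*Protocol article*

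**What the plan says.** Under Statistical methods (Clinical efficacy), each co-primary outcome is analysed by ANCOVA to "compare the mean differences of co-primary outcomes at 24 weeks follow-up between the intervention and TAU groups after adjusting baseline scores". The baseline scores are not itemised, and no other covariate is named. The natural reading is that each outcome is adjusted for its own baseline value.

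The two hypotheses differ in population. H1 (depressive symptoms) is tested "among postnatal mothers with EPDS scores ≥9 points in the intervention group as compared to those in the TAU group"; H2 (abusive behaviour) covers all mothers.

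Four other places bear on the choice of covariates:

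- Randomization: the four strata are formed from hospital and EPDS group (0–8 against 9 or more).
- Background: the risk factors listed for child abuse are "parental depression, anxiety and anger-hyperactivity, parent stress, poor parent–child interactions, and low social support".
- Sensitivity analysis: the main analysis uses complete cases under missing completely at random (MCAR). The authors suppose that initial depressive symptoms affect adherence, and they make baseline EPDS one of the weights in the dropout-weighted analysis.
- Table 2: EPDS, CTS-1, PHQ-9 and PSI-SF are all collected at enrolment.

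**The concern.** In three separate places the plan treats initial depression as important, yet the CTS-1 primary model apparently leaves it out. H2 pools women from both EPDS strata, so EPDS varies widely in that analysis and could explain part of the outcome variance. If it also predicts who drops out, a complete-case comparison that does not condition on it leans harder on MCAR than it needs to.

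The covariate that is used may also be a modest one. Eligibility is "Postnatal women who had given birth within 10 weeks of recruitment", so baseline CTS-1 describes behaviour towards a very young baby over a short time. That it predicts 24-week CTS-1 only weakly is plausible, but the document gives no correlation.

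At stake are a little precision and some robustness to dropout. Validity is not in question.

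**Working it through.** **1. Does the stated sample size depend on covariate adjustment?** For H1 the plan gives "effect size of the internet-based behavioural activation for postnatal depression as d = 0.55", significance level 0.05, 80% power, 85% follow-up and 128 women. Two-sided testing is assumed, because a one-sided test does not reproduce 128. A two-sample t-test needs 53 per arm (power 80.1%; 52 gives 79.3%). Then 53/0.85 = 62.4, rounded up to 63 per arm, or 126 in all. That is within two of 128 with no covariate credit, so the size does not rest on how prognostic the baseline score is.

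**2. H1 power before adjustment.** The plan recruits 150 high-EPDS women, more than the 128 that H1 needs. At 80% follow-up, 150 × 0.80 / 2 = 60 completers per arm. With d = 0.55, t-test power is 84.8% (85.4% by the normal approximation). At 85% follow-up (63.75 per arm) it is 86.9%.

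**3. H1 with added covariates.** The document gives no correlations, so these are scenarios. They take an R-squared of baseline EPDS for 24-week EPDS of 0.09 to 0.36 in unselected mothers, a 20% or 38% share at 9 or more (150/390 = 38%), and normal truncation. Power is by normal approximation with residual SD = √(1 − R²).

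| Completers per arm | Unadjusted | Baseline EPDS | + PHQ-9 and PSI-SF |
|---|---|---|---|
| 54.4 (128 × 0.85 / 2) | 81.8% | 82.6–87.3% | 83.5–91.9% |
| 60 | 85.4% | 86.1–90.3% | 86.9–94.2% |

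Within any one scenario the last step adds about 0 to 5 points. It adds essentially nothing when the extra scores are redundant with EPDS (for example 86.0% to 86.1%).

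**4. Pooled H2 power.** Weighting the plan's stratum effects by planned size, d = (150 × 0.50 + 240 × 0.40)/390 = 171/390 = 0.438. Completers per arm are 390 × 0.80 / 2 = 156. If added covariates explain a share r of the residual variance, the effect becomes d/√(1 − r) and the interval width is multiplied by √(1 − r). Power is by normal approximation.

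| Assumed r | Power, d = 0.438 | Power, assumed d = 0.30 | Interval width |
|---|---|---|---|
| 0 | 97.2% | 75.5% | 1.000 |
| 0.03 | 97.6% | 76.7% | 0.985 |
| 0.05 | 97.8% | 77.6% | 0.975 |
| 0.10 | 98.3% | 79.8% | 0.949 |

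At the plan's effects the gain is 0.4 to 1.1 points. If the true effect were 0.30, it would be about 1 to 4 points.

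**5. How much does selection at 9 or more weaken baseline EPDS in H1?** For a variable cut from below, R² in the selected group = R²u / (R²u + 1 − R²), where u is the ratio of selected to full variance.

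- Normal scores: u = 0.22 (20% share) or 0.30 (38% share), so an R² of 0.25 falls to 0.07 or 0.09.
- Right-skewed scores (rounded gamma on 0–30, mean 5 to 7, SD 4 to 5 with SD rising with the mean; 16% to 30% at 9 or more): u is about 0.72 to 0.77, so 0.25 falls only to 0.19 to 0.20. A less skewed case (mean 7, SD 4) gives 0.17.

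The answer turns on a distribution that the document does not report.

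**The case against.** The strongest reply is that nothing here is an error. ANCOVA on the outcome's own baseline is a standard, valid analysis of a randomised comparison. The phrase about baseline scores is not itemised, and a fuller covariate list may sit in an analysis plan not shown. Stratified randomisation already balances EPDS group between arms, and the weighted sensitivity analysis already addresses dropout related to EPDS. Every gain rests on assumed correlations and may be nil. Nearly all of this stands and limits the point to a suggestion. It remains true that the stated primary CTS-1 model does not use a variable to which the plan itself assigns prognostic and dropout roles.

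Three stronger readings are tempting and are not supported:

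- **That restricting H1 to EPDS 9 or more strips baseline EPDS of most of its predictive value.** This needs a normal distribution; skewed scores give a much smaller loss. Stratification also uses the most recent EPDS at recruitment, and the Discussion says that the timing of the baseline survey may differ. If the covariate is a separate measurement, truncation is indirect and weaker. PHQ-9, taken at the same time and overlapping with EPDS, would be indirectly restricted too.
- **That H1 is where the plan has least slack.** It has about 85% unadjusted power at 60 completers per arm.
- **That covariates are needed to rescue CTS-1 power.** Stratum-level power at 80% follow-up is 77.5% (high EPDS, d = 0.50, 60 per arm) and 78.7% (low EPDS, d = 0.40, 96 per arm). That shortfall comes from how dropout was applied: 64/0.80 = 80 and 100/0.80 = 125 per arm give 160 and 250, against 150 and 240. It is a separate matter, and H2 as worded covers all mothers.

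**Conclusion.** The point holds as a low-cost improvement. On the natural reading, the primary CTS-1 model omits baseline EPDS, and the plan's own strata, risk factors and dropout weights all argue for including it. In a randomised comparison a prespecified baseline covariate does not introduce bias of any consequence, and conditioning on EPDS makes the complete-case analysis less dependent on MCAR.

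The size is small. For pooled H2 it is about 1 power point or less at the plan's effects, with intervals 1.5% to 5% narrower, for an assumed partial R-squared of 0.03 to 0.10. For H1, further baseline scores add about 0 to 5 points, possibly none if PHQ-9 repeats what EPDS already says. The robustness gain cannot be quantified from the document. Neither the ANCOVA nor the stated sample size is shown to be wrong by this point.

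**What to change.** Before outcome data are seen, name the covariates:

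- CTS-1 ANCOVA (H2): baseline CTS-1 and continuous baseline EPDS, with baseline PSI-SF as an option.
- EPDS ANCOVA (H1): baseline EPDS, with baseline PHQ-9 as an optional precision covariate.
- Keep the model adjusted only for the outcome's own baseline as a supporting analysis for each.

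If the full analysis plan already lists these covariates, no change is needed. Otherwise the cost is a line or two of text and one degree of freedom per added covariate. All the scores are already scheduled at enrolment.

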**Paediatric**					
Height, body weight	Physical development	X		X	X
Type of nutrition (breast milk, formula, both, baby food)	Nutritional status	X		X	X
Attendance of well-baby visits at 1, 3, 6–7, 9–10 months)	Health check-up status	X		X	X
Immunization record (Hib, pneumococcus, DPT-IPV, rotavirus, BCG)	Immunization status	X		X	X
Use of inpatient and outpatient medical care for injuries, foreign body ingestion, burn, and drowning in the 3 months	Medical cost for injuries	X		X	X

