**Implementation**					
Implementation outcome scale for Digital Mental Health (IDMH) for users	Acceptability, appropriateness, feasibility, overall satisfaction, and harms			X	

*EPDS* Edinburgh Postnatal Depression Scale, *CTS-1* Conflict Tactics Scale, *PHQ-9* Patient Heatlh Questionnaire-9, *PSI-SF* Parent stress index-short form Japanese version, *MIBS-J* Mother-to-Infant Bonding Scale Japanese version, *EQ-5D-5L* EuroQol-5 dimension-5 level

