#### Physical assault

Maltreatment measures including both minor and major physical assault are measured with 9 physical assault items of CTS-1 [54–56], as mentioned in the psychological aggression section. The participants will be asked to answer the nine items on physical assault on a scale of 0 to 6, with a higher score indicating more severe physical assault.

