#### Health check-up attendance

Health check-up attendance will be evaluated by asking questions about whether children have attended well-baby check-ups at 3, 6, and 9 months (if applicable) during the 12-week and 24-week follow-up surveys.

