#### Immunization status

Immunization status will be evaluated by asking questions about whether children have completed immunization for Hemophilus influenzae type b, *Streptococcus pneumoniae*, diphtheria, tetanus, pertussis, and polio (DPT-IPV) during the 12–24 week follow-up surveys.

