#### Healthcare use for children

The healthcare use of children will be evaluated by asking questions about the inpatient and outpatient healthcare use for injuries, fractures, burns, foreign body ingestions, skin problems, or nutrition problems in the past 3 months. Healthcare questions will be administered during the 12–24 weeks of follow-up surveys.

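### Baseline-adjusted ANCOVA is fixed for every secondary outcome in Table 2, but five rows are nominal, yes/no or care-use measures, and the table omits physical assault and defines child healthcare use differently from the text

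*Protocol article*

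**What the plan says.** Under Statistical methods, Clinical efficacy, the protocol article gives a single rule for the secondary outcomes: "the ANCOVA will be conducted to compare secondary outcome measures (Table 2) between the TAU and intervention groups after adjusting baseline scores". It names no other model for them. The rule takes its list of outcomes from Table 2.

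Table 2 has eleven rows outside the co-primaries: five maternal, five paediatric and one implementation row. The paediatric rows include "Attendance of well-baby visits at 1, 3, 6–7, 9–10 months" and "Use of inpatient and outpatient medical care for injuries, foreign body ingestion, burn, and drowning in the 3 months", both marked as collected at enrolment, 12 weeks and 24 weeks.

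The outcome text describes some of these differently:

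- Attendance is asked at the 12- and 24-week surveys as "whether children have attended well-baby check-ups at 3, 6, and 9 months (if applicable").
- Immunisation is evaluated by "asking questions about whether children have completed immunization", again at follow-up.
- Child healthcare use covers "injuries, fractures, burns, foreign body ingestions, skin problems, or nutrition problems in the past 3 months".
- Physical assault has its own subsection among the secondary outcomes: "Maltreatment measures including both minor and major physical assault are measured with 9 physical assault items of CTS-1". In Table 2, CTS-1 appears only once, as the co-primary measure of psychological aggression.

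**The concern.** The article makes a positive statement about the method, so this is not detail left to an analysis plan. An analysis plan that followed the sentence would apply a comparison of adjusted means to outcomes that have no mean, or for which a mean is not the obvious summary. It would also ask for a baseline covariate that cannot carry information for some visits.

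The link to Table 2 matters as much as the model. Physical assault is the only direct measure of abusive behaviour besides the co-primary, in a trial whose second hypothesis concerns abuse. If Table 2 defines the analysis set, the article gives no analysis for it. Where the table and the text define one outcome in two ways, the choice between them stays open until the data are seen.

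**Working it through.** The documents give no figure to reproduce here, so the check sets the rule against each outcome.

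**Outcome type.** Table 2 rows outside the co-primaries:

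| Row | Type | Fits a baseline-adjusted mean comparison? |
|---|---|---|
| PHQ-9, PSI-SF, MIBS-J, EQ-5D-5L (4 rows) | scores | yes |
| Height and weight | SD scores, per the text | yes |
| Type of nutrition | four unordered categories | no; a mean is meaningless |
| Well-baby attendance | yes/no per visit | only as a risk difference |
| Immunisation | completed or not | only as a risk difference |
| Maternal care use | days of care | only as a mean difference; variance needs care |
| Child care use | events or days | only as a mean difference; variance needs care |
| Implementation scale for users | scores, 12 weeks only | no baseline exists |

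The count is 4 + 1 = 5 rows that fit, 5 that are not continuous scores, and 1 without a baseline: 5 + 5 + 1 = 11.

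**Baseline for attendance.** Inputs are recruitment usually at the 4-week postnatal visit (Procedure), birth within 10 weeks of recruitment (Inclusion criteria), and surveys at 12 and 24 weeks after program start. Program start is assumed to follow soon after recruitment. Infant age = age at recruitment + survey week; months = weeks × 7 / 30.4375.

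| Survey | Recruited at 4 weeks | Recruited at 10 weeks |
|---|---|---|
| Enrolment | 4 wk = 0.9 months | 10 wk = 2.3 months |
| 12 weeks | 16 wk = 3.7 months | 22 wk = 5.1 months |
| 24 weeks | 28 wk = 6.4 months | 34 wk = 7.8 months |

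At enrolment only the 1-month visit can have taken place. Visits at 3 months and later cannot have an informative baseline, although the Table 2 row is marked at enrolment. At the 24-week survey infants are about 6.4 to 7.8 months old, so the 9–10-month visit normally lies beyond follow-up.

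For immunisation and care use the evidence is weaker. Table 2 marks an enrolment assessment and the text mentions only the follow-up surveys. That is a conflict about timing and does not show that a baseline is impossible.

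**Table against text.**

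- Physical assault: a secondary outcome in the text, with no row in Table 2.
- Child healthcare use: drowning is only in Table 2; skin and nutrition problems are only in the text. Fractures are named only in the text but fall within the table's injuries.

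**The case against.** The strongest reply is that much of this is harmless. In a randomised trial of 390 women, a linear model on a yes/no item estimates a risk difference, and on days of care a difference in means. Both can be interpreted, and robust standard errors deal with the variance. Table 2 gives medical cost as the aim of the care-use rows, for which a mean difference is a natural target. This stands. A reader might infer that these comparisons are invalid, but the documents do not support that. They also say nothing about how many zeros the care-use data will contain. Only nutrition type cannot be compared meaningfully as written.

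A reader might also infer that the later-visit comparisons are inestimable. They are not: a baseline that is the same for everyone drops out, and the comparison between arms remains. The baseline wording is loose there, not fatal.

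The text's qualifier on the 9-month visit, "whether children have attended well-baby check-ups at 3, 6, and 9 months (if applicable"), already softens that point. What remains is that Table 2 does not carry it.

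Nor is physical assault certain to be lost. It is prespecified in the text with its items and scoring, and CTS-1 is in the table at all three time points. The defect is a missing row, which matters because the analysis sentence points to the table.

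Finally, it is tempting to say that the rule compares arms on a scale that only one arm can answer, "Implementation outcome scale for Digital Mental Health (IDMH) for users". That is an inference. The text says participants complete it and does not name an arm, and it is unclear whether implementation outcomes fall under a sentence headed Clinical efficacy.

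A condensed article may leave outcome-specific models to other documents. This one, however, states a rule, and the rule does not fit the outcomes it names.

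**Conclusion.** The point holds in a limited form. The stated rule does not suit five of the eleven rows: it is meaningless for nutrition type, and it is not the natural choice, though workable with care, for two yes/no outcomes and two care-use outcomes. The baseline term has nothing to adjust for at visits due from 3 months onward. Table 2 leaves out physical assault and disagrees with the text on child healthcare use.

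The co-primary tests, the sample size and the error control do not depend on any of this, so the consequence is confined to the secondary results. Within those it touches most of the child outcomes and the only other direct abuse measure. The age figures assume that the program starts soon after recruitment and that surveys are answered about when due. The classification of outcomes needs no such assumption.

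**What to change.** Replace the single sentence with rules by outcome type, and bring Table 2 into line with the text:

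- Keep baseline-adjusted ANCOVA for PHQ-9, PSI-SF, MIBS-J, EQ-5D-5L and growth SD scores.
- Use a binary-outcome model, such as logistic or modified Poisson regression, for attendance and immunisation.
- Use a categorical model for type of nutrition.
- For care use, choose either a count model or a mean difference with robust or bootstrap standard errors.
- Omit the baseline term where no baseline exists.
- Add CTS-1 physical assault to Table 2, with its time points, and to the secondary analysis.
- Settle one component list for child healthcare use across Table 2 and the text.
- Carry the text's age qualifier for visits into Table 2, given infant ages of about 6.4 to 7.8 months at the last survey.
- If implementation outcomes are meant to fall under this sentence, state that the user scale is summarised descriptively among program users, since it has no baseline.

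The cost is wording in the analysis section and Table 2. The text already describes collecting these items, so no new data should be needed. The child healthcare components and the physical-assault time points should be checked against the questionnaire in use, and the changes made before outcome data are compared by arm.
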